## Abstract

Procrastination is more than just a common human foible; it is a ubiquitous behavioral disorder that can negatively impact learning, productivity, and mental health. The psychological and neurological mechanisms underlying chronic procrastination are surprisingly complex, involving impairments in self-control, emotional regulation, and episode anticipation networks, and may lead to emotional distress, reduced self-confidence, and even physical symptoms that in turn can exacerbate procrastination. The aim of this proposed study is to investigate the clinical efficacy of acupuncture for university students with severe procrastination tendencies, to compare the efficacy of acupuncture to other potential interventions (Tai Chi and running exercise), and to examine the effects of acupuncture on cognitive functions related to procrastination. This parallel randomized controlled clinical trial will be conducted at the Third Affiliated Hospital of Henan University of Chinese Medicine, Henan Province, China. A total of ninety full-time college students will be randomly divided into three equal groups (acupuncture group, running group, and Tai Chi group). Each group will receive the assigned intervention for 30 min per session, 3 times per week on alternating weekdays, for a total of 4 weeks. The General Procrastination Scale (GPS) will serve as the primary outcome measure, while the Procrastination Assessment Scale for Students (PASS) and Physical Activity Rating Scale 3 (PARS-3) will be used as secondary outcome measures. Assessments using these outcome measures will be conducted at baseline (0 week) as well as after 2 and 4 weeks of intervention. Scalp electroencephalography (EEG) will be used to measure event-related potentials P300 and N200 during the Go/No-go Emotion Detection task and Task Initiation Delay Paradigm (TIDP) to investigate the impacts of these interventions on cognitive control and error detection abilities.

**Clinical trial registration:**
https://www.chictr.org.cn/showprojEN.html?proj=278360, identifier: ChiCTR2500105950.

## Introduction

Procrastination, defined as “the behavior of voluntarily postponing planned tasks despite being able to anticipate harmful consequences” (1), is a highly prevalent behavioral disorder worldwide. Procrastination is particularly prevalent among college students, with more than 70% admitting to academic procrastination, of which about 16% exhibit serious academic procrastination (2). Another survey of 22,896 college students found that more than 90% reported procrastination habits, of which more than 60% indicated that this habit negatively affected learning. Procrastination behaviors are also common among college students in their daily lives, such as delaying the completion of daily tasks and decision-making. Procrastination manifests as postponement, indirect avoidance, and inefficiency, and can result in emotional distress, physical symptoms, and reduced self-confidence. For example, procrastinators often put off completing tasks, potentially missing deadlines, wait until the last minute to begin a task on the grounds that it is “not urgent” or they are “waiting for inspiration” (3), often resulting in suboptimal work. Even after beginning a task, many individual with procrastination tendencies may prioritize other unimportant activities such as scrolling through mobile phones or playing video games to avoid work or study that requires their full concentration. These frequent distractions reduce work efficiency and quality. Missed deadlines and poor work may in turn lead to self-blame and guilt, creating a cycle in which procrastination weakens self-efficacy and self-confidence, and results in even greater tendencies for task avoidance and delay. Procrastination impairs learning and work efficiency, and can lead to an increase in psychological distress and reduced quality of life. The persistence of such behaviors can lead to a loss of individual productivity, and incur a socio-economic burden, as the World Health Organization estimates that procrastination costs more than US $1.2 trillion globally (1).

Procrastination is associated with a variety of mental health problems, including depressive symptoms, anxiety, and higher stress levels (4), which may reduce quality of life (5) and disturb both digestive function and sleep (6, 7). In addition, procrastination may negatively impact physical health directly by reducing the frequency of healthy behaviors such as exercise and healthy eating.

Procrastination can be understood as a failure of self-regulation and explained by the interplay of four variables: the value associated with completing an activity, the expectation to achieve that value, the time remaining to reach the desired value, and level of impulsiveness (8). The capacity for starting challenging tasks is strongly dependent on activities of the self-control system, emotion regulation system, and episode anticipation system (9). The dorsolateral pre-frontal cortex (dlPFC) is considered a major hub of the self-control system responsible for top-down cognitive control (10). In brain models, the range of the self-control system has been extended to the anterior cingulate cortex (ACC). A large body of evidence indicates that the ACC is capable of conflict monitoring and error signal reinforcement learning during the decision-making process. Although it is challenging to directly detect or measure ACC functions in self-control, it plays a role in regulating cognitive resources that are beneficial to the self-control process (11). A neuroimaging study by Chen and colleagues found that procrastination tendency was positively correlated with gray matter volume (GMV) in the left insula, ACC, and parahippocampal gyrus (PHC), negatively correlated with dlPFC GMV and ACC gray matter density, and positively correlated with cortical thickness and cortical complexity of the bilateral orbitofrontal cortex (OFC) (9). The dlPFC and ACC are part of an integrated cognitive control network, and deficits in cognitive self-control have been linked to increased vulnerability for neuropsychiatric disorders. It is thus reasonable to speculate that this comprehensive self-control network is a core negative regulator of procrastination (12, 13).

Dysfunction of the emotion regulation network results in difficulty controlling and suppressing negative emotions such as anxiety and stress when facing tasks, which in turn can lead to procrastination. When individuals are unable to properly manage negative emotions, they may choose to avoid or delay tasks to temporarily relieve inner discomfort (14). The specific emotion regulation strategies employed by the individual can also influence procrastination behavior. Cognitive reappraisal strategies can help individuals view tasks from a positive perspective and reduce the generation of negative emotions, thereby reducing the tendency to procrastinate. On the other hand, expressive inhibition strategies only temporarily suppress emotional expression, but do not change the individual's cognition and emotional experience of the task, so any improvement in procrastination behavior will ultimately be limited (15). The emotional processes induced by task involvement are core factors influencing procrastination, so it is expected that procrastination behavior will be associated with the morphological properties and activity patterns of the emotional regulation network. Indeed, positive correlations were found between procrastination and GMV of insular lobes, GMD of the OFC, and complexity of the OFC (9).

The cognitive mechanisms underlying procrastination are well explained by emotion regulation theory. Simply stated, in order to avoid task-induced short-term negative emotions, individuals sacrifice long-term task rewards for more immediate positive experiences, leading to procrastination (12, 16). As a key subcortical region of the prominence network, the insula plays an important role in social emotions and disgust in response to task-evoked signals, and insular activity is strongly correlated with emotional downregulation and subsequent sequela. The function of the OFC is thought to be comparable to that of the insula, contributing to the regulation and further re-evaluation of negative emotions as part of the general emotion regulation network (17). The essence of procrastination is flawed intertemporal decision-making, which refers to an individual's choice after weighing “immediate satisfaction from not doing something now” against “future benefits from completing it later”. The core flaw lies in the evaluation of “the future”. Future evaluation is based on self-cognitive projections formed from past experiences, supported jointly by the parahippocampal cortex, which integrates past memories, and the ventromedial pre-frontal cortex, which simulates future events. An individual's expectations for the future directly influence procrastinatory behavior; vague or negative outlooks tend to promote procrastination while clear goals can reduce it. Moreover, the “phased future expectation” that breaks down long-term tasks into phased small goals can constrain the “temporal discounting effect”, a psychological bias where humans tend to underestimate long-term benefits. Thus, clarifying short-term benefits cane enhance long-term value, thereby reducing the urge to procrastinate (12, 18). The PHC is a central node of the medial temporal lobe (MTL) and is essential for episodic memory and episodic futuristic thinking. The ventromedial (vm) PFC also plays a role in episodic future thinking, especially in future-focused and goal-oriented anticipation (19, 20). While the MTL encodes the retrospective details of experiences, the vmPFC contributes to episodic future thinking by generating a more abstract imagination after the individual's own self-referential process. For this, the vmPFC makes use of updated self-knowledge (experience) simulations to deliberate on the process of future task costs (including emotional distress), outcomes (value), and work load. In this theoretical framework, one root cause of procrastination is a failure in belief related to imagining and evaluating the true future value of tasks, which is associated with structural abnormalities in the neural network responsible for envisioning future scenarios. Among these failures is a flaw in “episodic future thinking,” defined as the ability to imagine future task outcomes supported by the “episodic prospection network”. The core brain regions of this network include the parahippocampal cortex (PHC), which integrates past experiences to provide materials for imagining the future, and the ventromedial pre-frontal cortex (vmPFC), which assesses the value of future outcomes. Under normal circumstances, the two work synergistically to help individuals correctly recognize the long-term value of tasks and reduce procrastination. However, if the underlying circuitry is abnormal due to disruptions in cellular organization (or resultant abnormal morphology), the PHC may not provide a realistic basis for imagining the future, and the vmPFC may not accurately evaluate the future value of tasks. Ultimately, this impairment makes it difficult for individuals to perceive the long-term significance of tasks, leading to immediate task avoidance (18).

Acupuncture, a core intervention in this study, has its potential value for ameliorating procrastinatory behavior supported by modern neurophysiological research (21). We hypothesize that it exerts regulatory effects by targeting the core neural networks and psychological processes underlying procrastinatory behavior (9). Modern neurophysiological studies have fully confirmed that acupuncture can modulate the activity of key brain regions and neural networks associated with procrastination (22). Specifically, acupuncture stimulation at acupoints such as Baihui (GV20), Sishencong (EX-HN1), Neiguan (PC6), and Zusanli (ST36) can enhance the functional activity of the dorsolateral pre-frontal cortex (dlPFC) and anterior cingulate cortex (ACC)—the core nodes of the cognitive control network—thereby improving the top-down cognitive control, conflict monitoring, and error correction abilities that are deficient in individuals with high procrastination tendency (23). In addition, acupuncture can regulate the activity of the insula and orbitofrontal cortex (OFC) within the emotion regulation network, reduce the overactivation of the brain in response to negative emotional stimuli, and enhance individuals' ability to suppress and regulate negative emotions such as anxiety and stress when confronted with tasks, thus breaking the vicious cycle of emotional avoidance that triggers procrastination (24). Furthermore, acupuncture has been proven to promote neuroplasticity and improve the connectivity of the episodic prospection network consisting of the parahippocampal gyrus (PHC) and ventromedial pre-frontal cortex (vmPFC) (25). This effect helps optimize the brain's ability to envision future task outcomes and evaluate long-term values, thereby alleviating the intertemporal decision-making deficits that constitute the essence of procrastinatory behavior. Clinical and experimental studies have also confirmed that acupuncture can effectively improve attention, executive function, and impulse control in diverse populations, and these enhancements in cognitive functions are directly relevant to the correction of procrastinatory behavior (26).

The theory of planned behavior (TPB) is one of the most successful theoretical models for explaining the relationship between intention and behavior (including physical activities such as exercise), and can assist in elucidating the mechanism underlying the effects of physical activity on academic procrastination (27–29). The core propositions of the theory are that intentions can directly determine behavior, that behavioral attitudes, subjective norms, and perceived behavioral control are the three main predictors of behavioral intention intensity, and that the more positive an individual's attitude toward the goal, the stronger the subjective norm, the greater the perceived behavioral control, the stronger the intention to perform the goal-oriented behavior, and the more likely the individual is to participate in the behavior (i.e., without delay) (30, 31). Empirical studies have shown that TPB can explain nearly 40% of the variance in physical behavior, and all predictors of TPB can significantly predict the state of college students' participation in physical activity (32, 33). Thus, TPB provides a robust framework for procrastination research. A study examining procrastination behavior by college students and the efficacy of physical intervention based on the TPB framework concluded that physical activity has a negative predictive effect on procrastination behavior. As proposed by American psychologists Burka and Yuen in their book Procrastination: why you do it and what to do now (34, 35), physical activity can maintain an individual's physical health and enhance their courage to face postponed tasks, thereby reducing procrastination (36). In accord with this notion, Tao et al. reported a significant negative correlation between procrastination and physical activity among a cohort of 610 college students (37).

Tai Chi is a form of combined physical and cognitive training that may be particularly effective against procrastination. Tai Chi movement combined with cognitive training was reported to delay the progression of mild cognitive impairment (MCI) to dementia more effectively than cognitive training alone (38). Tai Chi combined with mindfulness training was also reported to enhance PFC activity and reduce decision hesitancy at the initiation of tasks (e.g., the “Should I start working or procrastinate” conflict). Moreover, Tai Chi with mindfulness training has also been found to improve Conners scale attention scores (*p* < 0.05) in parallel with the intensity of training (39, 40).

Event-related potentials (ERPs) are electroencephalographic waveforms reflecting specific neural processing events, including sensory perception, attentional allocation, and decision-making. Multiple studies have reported greater P200 amplitude by high procrastinators during the time delay and reward processing phases of delayed reward tasks, suggesting that these individuals allocate attentional resources more slowly and that motivationally driven attention to this information is elevated compared to low procrastination individuals (41, 42). In addition, while there was no significant difference in P300 amplitude between high and low procrastination individuals in the reward processing stage, the P300 amplitude of individuals with high procrastination was larger in the time delay processing stage, indicating higher cognitive load when processing time-delayed information. Alternatively, the P300 amplitude of individuals with low procrastination was larger during the reward processing phase, indicating a higher cognitive load when processing reward information (43, 44). Thus, the abnormal P300 component exhibited by high procrastination individuals indicates greater sensitivity to time delay in reward-based tasks, resulting in a greater propensity to choose smaller immediate rewards over greater delayed rewards, consistent with temporal motivation theory (TMT) (45, 46). This tendency may also be related to greater impulsivity.

The N200 ERP component usually appearing 160–240 ms after the presentation of a stimulus is primarily reflective of early attentional and cognitive processing, especially attentional allocation, and changes in N200 latency and amplitude are closely related to response inhibition and other aspects of cognitive control over behavior. Abnormalities in N200 among high procrastinators suggest a reduced ability to monitor task conflicts, making it difficult for these individuals to suppress distracting stimuli or prioritize tasks with perceived low short-term value (but possible higher delayed value) (47–49). One study reported a significant difference in N200 between the high and low procrastination groups as well as significant right lateralization of the visual ERP N1 among low procrastination individuals compared to the high procrastination group, suggesting that lower-level procrastinators are more alert to early information processing, while high procrastinators devote less attentional resources to tasks and show more impulsiveness and less control over immediate events (12). Patients with attention deficit hyperactivity disorder (ADHD) have also demonstrated a prolonged N200 latency, reflecting an inadequate allocation of attentional resources, and procrastination overlaps symptomatically with ADHD (including difficulty initiating tasks). Moreover, it is speculated that abnormalities in N200 may reflect similar underlying neural mechanisms (50, 51).

### Objectives

The purposes of the proposed study are to evaluate the clinical efficacy of acupuncture and exercise (running, Tai Chi) for reducing procrastination and to explore the underlying neurocognitive mechanisms by measuring ERP changes.

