## Methods/design

### Study setting

This parallel randomized controlled clinical trial will be conducted at Third Affiliated Hospital of Henan University of Chinese Medicine, Henan Province, China, according to the principles outlined in Consolidated Standards of Reporting Trials (CONSORT), Standards for Reporting Interventions in Acupuncture Clinical Trials (STRICTA), and Standard Protocol Items: recommendations for Interventional Trials (SPIRIT) guidelines (Figure 1). Ninety full-time college students will be randomly and equally assigned to acupuncture, running, and Tai Chi groups. The allocated intervention will be conducted for 30 min, 3 times per week on alternating weekdays for a total of 4 weeks (w). The General Procrastination Scale (GPS) will be used as the primary outcome measure, with the Procrastination Assessment Scale for Students (PASS) and Physical Activity Rating Scale 3 (PARS-3) used as secondary outcome measures. Outcome measures will be conducted at baseline (0 w) and after 2 and 4 weeks of intervention. In addition, P300 and N200 will be measured by scalp EEG during the Go/No-go Emotion Detection task and Task Initiation Delay Paradigm (TIDP) to observe the effects of these interventions on cognitive control and error detection abilities.

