### Recruitment

The study will recruit participants with procrastination from the Dongming Road Campus of Henan University of Traditional Chinese Medicine through posters stickers and online advertisements. Candidates who meet the inclusion criteria, do not meet any exclusion criteria, and agree to participate by providing written informed consent will be enrolled until the preset maximum sample size (n = 90) is reached. Additionally, 30 healthy subjects will be recruited as controls. The healthy control group is included to provide normative behavioral and electrophysiological reference values, rather than to serve as a treatment control for intervention effects.

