#### Inclusion criteria

Preset study inclusion criteria are as follows:

Full-time university student;GPS score ≥ 70 points;No psychotropic drug intake or related acupuncture treatment within the past 30 days;Providing informed consent.

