### Healthy control group

The healthy control group will not receive any intervention. Both GPS/PASS scales and ERP (P300, N200) under Go/No-go emotion task and TIDP will be collected at baseline”.

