## Outcomes

### Primary outcome

General Procrastination Scale (GPS) will be used as the primary outcome measure. The GPS is one of the most widely used and validated trait procrastination scales and has demonstrated good applicability for Chinese college students. It consists of 20 items scored on a 5-point Likert scale from “strongly disagree” (1 point) to “strongly agree” (5 points), and covers multiple domains including academic activities and activities of daily living (52). Note that higher scores on certain items are indicative of greater procrastination while higher scores on others are indicative of lower procrastination tendency, so some item scores are reversed before summation. After appropriate reversal, a higher total score is indicative of greater procrastination tendency, with a score between 20 and 49 points indicating low, 50–69 moderate, and 70–100 high procrastination. Xue and colleagues reported a Cronbach's α coefficient of 0.807 and a test–retest correlation coefficient of 0.756 after 4 weeks, indicating good internal consistency and reliability (53). Exploratory and confirmatory factor analysis revealed a two-factor structure consisting of active avoidance and lack of planning, and the model fitting effect was good (CFI=0.914, TLI=0.901, RMSEA=0.069, SRMR = 0.072). The GPS was also positively correlated with total scores on the Irrational Procrastination Scale and the Academic Burnout Scale (r = 0.753, 0.677, all *P* < 0.001), supporting good reliability and validity (54).

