### Data analysis

The primary analysis will be conducted using a linear mixed-effects model, with fixed effects for group (acupuncture, running, Tai Chi), time (baseline, week 2, week 4), and their interaction, and a random intercept for participants to account for within-subject correlation due to repeated measurements. Baseline GPS score, age, sex, and baseline ERP indices will be included as covariates to control for inter-individual variability in procrastination-related traits.

This mixed-effects modeling framework constitutes the primary analytic strategy and will be implemented under the intention-to-treat (ITT) principle, allowing inclusion of all available observations without imputing missing values, under a missing-at-random assumption.

Prior to model fitting, distributional characteristics of continuous variables will be assessed using the Shapiro–Wilk test. Descriptive comparisons of baseline demographic and clinical characteristics will be performed using analysis of variance (ANOVA) or the Kruskal–Wallis test for continuous variables, and chi-square or Fisher's exact tests for categorical variables, as appropriate, to ensure baseline comparability between groups.

Secondary and exploratory analyses may include pairwise comparisons or non-parametric tests (e.g., Mann–Whitney *U*-test or Wilcoxon signed-rank test) where appropriate for specific outcomes or sensitivity checks. For outcomes with repeated measurements that meet parametric assumptions, repeated-measures ANOVA may be used as a supplementary analysis; otherwise, non-parametric alternatives such as the Friedman test will be applied.

Sensitivity analyses will be conducted to evaluate the robustness of the primary findings, including per-protocol analyses restricted to participants with adherence ≥80% and models incorporating adherence (number of completed sessions) as a continuous covariate.

For secondary outcomes and exploratory ERP analyses involving multiple indices or task conditions, false discovery rate (FDR) correction will be applied within pre-defined families of related comparisons. Statistical significance will be defined as a two-sided *P*-value < 0.05. All analyses will be performed using PASS 18.0, with statistical consultation provided by an institutional biostatistician.

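### The stated objective is efficacy of each intervention, but with three active arms the design can show only which arm does better

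*Protocol article*

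**What the plan says.** The Objectives section gives the purpose as "to evaluate the clinical efficacy of acupuncture and exercise (running, Tai Chi) for reducing procrastination", together with exploring mechanisms through ERP change. The Abstract lists the efficacy of acupuncture and its comparison with Tai Chi and running as separate aims, so efficacy is not simply another word for the comparison.

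On the arms, Study setting states: "Ninety full-time college students will be randomly and equally assigned to acupuncture, running, and Tai Chi groups". Thirty healthy students are added, but Recruitment says they supply reference values "rather than to serve as a treatment control for intervention effects". The Healthy control group section adds: "The healthy control group will not receive any intervention", and describes their scales and ERPs as collected at baseline.

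Entry requires "GPS score ≥ 70 points", on the scale that is also the primary outcome. Under Primary outcome, that scale is reported to have "a test–retest correlation coefficient of 0.756 after 4 weeks".

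Data analysis makes a linear mixed model with group, time and their interaction the primary analysis. A later paragraph on secondary and exploratory analyses offers pairwise comparisons and the Mann–Whitney and Wilcoxon signed-rank tests. It then says that, where repeated outcomes do not meet parametric assumptions, "non-parametric alternatives such as the Friedman test will be applied". Expected results anticipates that, after any of the interventions, N200 and P300 will shift in the direction of healthy values, and treats such shifts as possible markers of effectiveness.

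**The concern.** The efficacy of an intervention is a contrast with what would have happened without it. No randomised arm supplies that contrast. The arms can be compared with one another, but if all three change alike, the trial cannot tell three useful interventions from three that do nothing.

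The stated objective could then be answered only from change over time within an arm. In this trial that change has causes other than treatment. Participants know what they receive (Blinding section), they complete the same self-report scale repeatedly, and they are admitted because they scored high on it. The signed-rank and Friedman tests are tests of change over time with no group factor, so they lend themselves to this reading. The article does not mention regression to the mean and does not confine efficacy conclusions to contrasts between arms.

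**Working it through.** **1. What the trial is sized for.** The Sample size section uses a one-way ANOVA of three groups with f = 0.40, α = 0.05 and power 0.90. With noncentrality N·f² and degrees of freedom 2 and N − 3, power is 0.895 at 27 per arm and 0.907 at 28. The stated 27 is therefore reproduced to within one participant per arm, and 27/(1 − 0.10) = 30. The sizing concerns a difference among the active arms, not efficacy against no treatment.

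**2. Inputs for change under no effect.** From the article: cut-off 70, r = 0.756 over 4 weeks (the length of the intervention), and 27 to 30 per arm. Assumed, because the article does not give them: student GPS mean μ of 50 to 60, SD σ of 8 to 12, normal scores with the same mean and SD at both times, and the screening score used as the 0-week score.

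**3. Formulas.** Let a = (70 − μ)/σ and λ = φ(a)/(1 − Φ(a)).
- Mean at entry = μ + σλ
- Expected fall with no effect = (1 − r)σλ
- Variance of change = (1 − r)²·Var(entry score) + σ²(1 − r²), where Var(entry score) = σ²[1 − λ(λ − a)]
- Probability that a two-sided 0.05 paired t-test is significant: noncentral t with noncentrality √n × fall/SD of change

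**4. One case in full (μ = 55, σ = 10).** a = 1.5 and λ = 1.939. Mean at entry = 55 + 19.4 = 74.4. Fall = 0.244 × 19.39 = 4.73. SD of change = 6.61. With n = 30, noncentrality = 5.477 × 4.73/6.61 = 3.92 and the probability is 0.966. Simulation at n = 30 gives 0.97 for the paired t-test and 0.96 for the signed-rank test.

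**5. Range, with no treatment effect.**

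| Mean / SD | Fall | SD of change | n = 27 | n = 30 |
|---|---|---|---|---|
| 50 / 8 | 5.51 | 5.27 | 0.999 | >0.99 |
| 50 / 10 | 5.79 | 6.60 | 0.992 | 0.996 |
| 50 / 12 | 6.09 | 7.93 | 0.970 | 0.982 |
| 55 / 8 | 4.42 | 5.28 | 0.987 | 0.993 |
| 55 / 10 | 4.73 | 6.61 | 0.947 | 0.966 |
| 55 / 12 | 5.06 | 7.95 | 0.890 | 0.921 |
| 60 / 8 | 3.37 | 5.30 | 0.890 | 0.921 |
| 60 / 10 | 3.72 | 6.64 | 0.801 | 0.843 |
| 60 / 12 | 4.08 | 7.97 | 0.726 | 0.773 |

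With 30 per arm, the probability that all three arms show a significant fall is the last column cubed: 0.773³ = 0.46 at the lowest and above 0.99 at the highest.

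**6. The randomised contrast.** The expected fall in step 3 depends on r, μ, σ and the cut-off, none of which differs by arm. It therefore cancels in expectation from the group-by-time term.

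**7. ERPs.** Students are selected on GPS, not on ERPs, so this calculation does not carry over. The difficulty there is that no untreated repeat recording is described against which a shift could be judged.

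**The case against.** The strongest reply is that this is an active-comparator trial, which is a legitimate design. The Abstract states the comparative aim, the sample size rests on a difference among arms, and the primary model tests it. The signed-rank test is an optional example and is not assigned to GPS. No sentence says that within-arm change will be reported as efficacy. All of this stands. It shows that the machinery fits the comparison, but it does not narrow the objective, which is worded as efficacy of each intervention.

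A reader might infer more: that GPS cut off at 70 must fail the Shapiro–Wilk test, that the Friedman test then takes over, and that the randomised comparison is never tested. The article does not support this. The mixed model is primary without any condition on normality. The Friedman test stands in for a supplementary repeated-measures ANOVA and is itself only an example. The same paragraph lists comparisons between arms, and no rule ties a test of baseline GPS to a change of method.

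The size of the fall is also open to challenge. The population mean and SD are assumed. The schedule figure is not shown, so a 0-week GPS taken separately from screening cannot be excluded. Such a baseline would remove much of the regression to the mean, but not natural course, expectation or retest effects.

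**Conclusion.** The concern holds as a mismatch between the objective and what the design can show. The trial can say which of three active interventions does better. It cannot say that any of them reduces procrastination, or that ERP movement towards healthy values is a treatment effect.

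Under the stated assumptions, a GPS fall of about 3.4 to 6.1 points is expected with no effect, and a single-arm paired test would be significant with probability of about 0.73 to above 0.99. As a yardstick, the pilot's week-8 arm means differ by 38.2 − 32.5 = 5.7 and 41.6 − 38.2 = 3.4 points. That the design lacks an untreated comparator needs none of these assumptions.

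Two further inferences should not be drawn. The primary GPS analysis is not biased by the selection and is not displaced by the Shapiro–Wilk or Friedman wording. Nor does the article commit to reporting ineffective interventions as effective; it leaves the door open by not restricting the claim.

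**What to change.** - Restate the objective and the planned conclusions as the relative efficacy of acupuncture versus running and versus Tai Chi.
- State that within-arm change, and movement of ERPs towards healthy-control values, are descriptive and not evidence of efficacy.
- In the secondary and supplementary part of Data analysis, replace the signed-rank and Friedman tests with a method that compares arms when parametric assumptions fail, for example rank-based ANCOVA or a bootstrap of the week-4 contrast.
- State whether the 0-week GPS is taken separately from the screening GPS, so that readers can judge how much regression to the mean to expect in the descriptive results.

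The cost is wording and a narrower claim; the sample size and the primary model stay as they are. Keeping the wider objective would instead require a randomised non-active comparator and a new sample size.
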